**Figure 2 figure2:**
[figure not shown]
Study flowchart for phase 2. DBI: Decisional Balance Inventory; SEE: Self-efficacy for Exercise; SOC: Stages of Change; T2D: type 2 diabetes; WC: waist circumference; WEL-Q: Weight-efficacy Lifestyle Questionnaire.

#### Study Population

The target population is patients with T2D aged 20-60 years old, with a BMI of more or equal to 23 kg/m^2^, who are not ready to act for weight loss. Study participants will be selected via purposive sampling method to ensure homogeneity between the 2 arms.

#### Participants Recruitment

The patients with T2D, who come for a routine appointment at the selected health clinics during the recruitment period will be approached, given the Patient Information Sheet (PIS) about the study, and invited to participate. If they are willing to participate, they will be screened by the investigators to determine their eligibility based on the inclusion and exclusion criteria. Then, written informed consent will be obtained from those who are eligible. Participants from the intervention arm will be given a username and password to access the Chance2Act intervention, whereas participants from the control arm will continue the existing health education module in the health clinic.

#### Eligibility Criteria

The patients with T2D aged 20 to 65 years old who fulfill all the following inclusion criteria will be included (1) BMI of more or equal to 23kg/m^2^; (2) in the precontemplation, contemplation, or preparation stage of change based on the s-weight questionnaire [19]; (3) able to understand, read, and write in the Malay language; (4) have access to any electronic device with internet service; (5) able to understand information and perform tasks in the digital environment, especially website; and (6) have at least 1 adult family member who is living in the same household.

Patients who fulfill any of the following criteria will be excluded (1) patients who are pregnant; (2) patients with advanced comorbidity and mental conditions that will affect participation and understanding of the study protocol, for example, vision problem, physically unfit to stand up and walk, advanced heart failure or cancer, and schizophrenia; and (3) patients who die or are transferred out to other health clinics during the study period.

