#### Delivery of the Chance2Act Intervention

The Chance2Act intervention will be delivered to the individual participants by the investigators. Participants will be given the Chance2Act website using their login account and password. Access to the website is free of charge. The intervention will comprise 4 main modules and will be delivered in sequence. Each module will take approximately 2 weeks to be completed. The sequence of the intervention was developed based on the Process of Change construct of the TTM [21].

The baseline measurements will be taken before the initiation of the intervention. Follow-up will be done by the investigator after the completion of the first 2 modules, approximately at week 5, and after the completion of the whole package of the intervention, at week 9. In addition, participants can seek help from the investigators to navigate through the functions of the Chance2Act website through the built-in messaging system.

The Chance2Act is a tailored intervention whereby the participants will receive personalized coaching about their weight-related behavioral problems to boost their motivation via the built-in messaging system. The principal investigator will actively monitor the progress of each participant and intervene according to the health education module. Information will be given through text on the website, sets of infographics, animations, and videos. Health quizzes will be conducted to assess the comprehensibility of the module. They will be given printed materials such as weight loss checklists and dietary and exercise weekly plan templates to assist their weight loss journey. Each participant will have at least 1 adult family member to join as part of the intervention modules. The family members will be guided on the ideal way to fully support the participants’ efforts for weight loss. They will receive clear information on their role during the weight loss journey.

Participants are expected to finish each module in 2 weeks and give the required feedback and responses at the end of the module accordingly. Follow-up will be done by the investigators. Participants who did not comply with the follow-up requirements will be considered a loss to follow-up. Data analysis will be by the intention-to-treat (ITT). There is no specific concomitant care and intervention that are permitted or prohibited during the trial.

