### Data Management and Statistical Analysis

For phase 1, the data will be entered in Microsoft Excel (Microsoft Office 365) and ready for analysis. The content validity will be assessed by the experts’ ratings. The CVI will be assessed based on 2 indices, the Item-level Content Validity Index (I-CVI) and Scale-level Content Validity Index (S-CVI). The criteria that will be assessed are mainly content relevance. The I-CVI will reflect each item or intervention activity relevancy, whereas S-CVI will reflect the overall module relevancy. Then, the face validation will be determined based on the FVI. Similarly, the FVI will be assessed based on 2 indices, the Item-level Face Validity Index (I-FVI) and the Scale-level Face Validity Index (S-FVI). The criteria that will be evaluated are the module clarity, simplicity, and ambiguity. For both CVI and FVI, the results of at least 0.83 will be considered acceptable [31,32].

For phase 2, the data will be entered into IBM SPSS Statistics (version 27; IBM Corp). Each CRF will be given a unique identifier. Screening for missing, redundant data or wrong coding will be done. The investigator will try to contact the participants to complete the missing data via telephone. Then, any remaining missing data will be dealt with an appropriate missing data handling method. For redundant data, only 1 data will be selected. The wrongly coded data will be corrected accordingly based on the CRF. Then, the data will be ready for analysis.

For the descriptive statistics, the normality tests will be used to determine the distribution of the data. The normally distributed will be described by using mean and SD, whereas not normally distributed data will be described by using the median and IQR. The categorical data will be presented by using frequency and percentage.

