To determine the homogeneity between the intervention and control group, an independent *t* test and chi-square test will be used to compare the demographic characteristics of the participants. The ITT analysis will be applied to measure the effectiveness of the Chance2Act intervention on the primary and secondary outcomes. The analysis models are within-group differences and between-group differences. The Generalized Estimating Equations (GEE) will be used as statistical analysis. A *P* value of less than .05 is considered statistically significant with 95% CI. Interim analysis will be conducted at T1 which is estimated at week 5. However, only certain outcome measures will be analyzed as predetermined in the phase 2 study flowchart.

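### Excluding patients for death or transfer during the study contradicts intention to treat, and the compliance-based rule for loss to follow-up could fall on one arm only

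*Protocol article*

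**What the plan says.** Under Eligibility Criteria, the third exclusion criterion covers "patients who die or are transferred out to other health clinics during the study period". Under Participants Recruitment, patients who are willing to take part are approached at a routine appointment, and "they will be screened by the investigators to determine their eligibility based on the inclusion and exclusion criteria"; written consent comes after that.

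Under Delivery of the Chance2Act Intervention, follow-up is placed after the first two modules (about week 5) and after the whole package (week 9). A later paragraph of that section opens: "Participants are expected to finish each module in 2 weeks and give the required feedback and responses at the end of the module accordingly". It then says that the investigators do the follow-up, and continues: "Participants who did not comply with the follow-up requirements will be considered a loss to follow-up". The next sentence states that analysis is by intention to treat.

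Under Data Management and Statistical Analysis the commitment is repeated: "The ITT analysis will be applied to measure the effectiveness of the Chance2Act intervention on the primary and secondary outcomes". The same section plans telephone contact to complete missing data, says that "any remaining missing data will be dealt with an appropriate missing data handling method", and names GEE as the analysis. Study Outcome schedules all measures in both arms at baseline, week 5 and week 9.

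**The concern.** Intention to treat means that everyone enrolled is analysed in the arm to which they belonged at entry. A criterion met only by something that happens later takes people out of that set after the fact. Here the clinic is the arm, so a transfer means leaving the site that defines a participant's group. That is a reason to look for the outcome elsewhere, not a reason to remove the person.

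The second matter is how loss to follow-up is defined. It should turn on whether the outcome was obtained. The article makes it turn on compliance, in a section about delivering the intervention and next to tasks that controls do not have. The primary outcome is movement into the action stage. People who stop engaging with a readiness programme are plausibly less likely to have moved. If such people go unmeasured or are dropped in one arm only, that arm's proportion ready rises without any effect of the intervention.

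**Working it through.** **1. The exclusion criterion against intention to treat.** No arithmetic is needed.
- Screening against the inclusion and exclusion criteria precedes consent (Participants Recruitment).
- Death or transfer during the study period cannot be known at that time.
- The criterion can therefore operate only on people already enrolled.
- Removing them is incompatible with both intention-to-treat statements.

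The article gives no expected number of deaths or transfers. Each removal is 1/65 = 1.5% of an arm at the Methods target of 65, or 1/62 = 1.6% at the Abstract's 62. The criterion applies to both arms and no imbalance is stated, so no direction of bias follows.

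**2. What the loss rule could do.** The planned effect is a 30-point difference with 44 per arm before attrition; the arm rates are not given. The Kelsey formula with two-sided alpha 0.05 (assumed) and 80% power is n = (1.960 + 0.842)² × 2 × p̄(1 − p̄) / 0.30². At 30% versus 60%, p̄ = 0.45 and n = 7.85 × 0.495 / 0.09 = 43.2, rounded up to 44. The stated 44 reproduces at the assumed pairs from 30% versus 60% to 40% versus 70%. A base rate of 35% is therefore a reasonable illustration, though still an assumption.

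Let p be the true proportion ready in both arms (no effect), f the fraction of the intervention arm left out, and q the proportion ready among those left out. Controls lose nobody. The observed intervention proportion is (p − f·q)/(1 − f). With p = 0.35:
- f = 0.20, q = 0.15: (0.35 − 0.030)/0.80 = 0.400, or +5.0 points
- f = 0.30, q = 0.15: (0.35 − 0.045)/0.70 = 0.436, or +8.6 points
- f = 0.40, q = 0.15: (0.35 − 0.060)/0.60 = 0.483, or +13.3 points
- f = 0.20, q = 0.25: (0.35 − 0.050)/0.80 = 0.375, or +2.5 points
- f = 0.40, q = 0.10: (0.35 − 0.040)/0.60 = 0.517, or +16.7 points

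The same formula shows when the bias disappears or reverses:
- Loss unrelated to readiness (q = p): (p − f·p)/(1 − f) = p, so no bias.
- The same f and q in both arms: equal observed proportions, so no bias.
- People kept and counted as not ready, with loss unrelated to readiness: −f·p, or −7 points at f = 0.20 and −14 points at f = 0.40.

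**3. Consequence for the test, under the same one-sided loss.** Take p = 0.30 and f = 0.40, and use a normal approximation for two proportions. At 65 per arm, 39 remain in the intervention arm.
- Those left out move at half the rate (q = 0.15): 0.40 against 0.30, +10 points. The chance of a falsely significant benefit is about 18%.
- None of those left out has moved (q = 0): 0.50 against 0.30, +20 points. The pooled SE is 0.0981 and the unpooled SE 0.0982, so Φ((0.20 − 1.96 × 0.0981)/0.0982) = Φ(0.08), about 53%. At 62 per arm it is about 51%.

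The nominal chance in that direction is 2.5%.

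**The case against.** A fair defence of the criterion is that it is a withdrawal rule placed under the wrong heading. Follow-up lasts about nine weeks and advanced heart failure and cancer are excluded, so few people may be affected. The likely small size stands. The conflict remains, because the text calls these people excluded and the analysis section promises not to exclude them.

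The defence is stronger on the loss rule. The sentence just before it concerns follow-up by the investigators, and follow-up is elsewhere the week-5 and week-9 assessments, which both arms have. On that reading the rule treats the arms alike. Nothing in the article says that those lost leave the analysis. The next sentence commits to intention to treat, and telephone recovery and missing-data handling are planned. All of this stands, so the rule is ambiguous but does not contradict the analysis plan.

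A reader might go further and infer that the analysis is per-protocol under an intention-to-treat label, that the comparison is biased toward benefit, or that an unweighted GEE on the remaining data makes it invalid. The documents do not support these readings. They remove nobody for non-compliance and specify no complete-case GEE, and the missing-data method may properly sit in the analysis plan. The 40% attrition behind the larger illustrations is planned per arm, not for the intervention arm alone.

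**Conclusion.** The third exclusion criterion contradicts the stated intention-to-treat analysis and should not stand. This follows from the article's own text and needs no assumption. Its numerical effect cannot be estimated from the article and has no evident direction.

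The definition of loss to follow-up is defective because it rests on compliance and can be read to cover tasks that only one arm has. Bias toward benefit would require three things together: the rule includes module tasks, the people it labels are not measured or are dropped, and they are less often ready than the rest. Under those conditions and the assumed rates above, the spurious difference is 2.5 to about 17 points at a 35% base rate. Without them it is zero or can be negative. The article makes the conditions plausible but does not establish them.

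**What to change.** - Delete the third exclusion criterion. Keep every enrolled participant in the intention-to-treat set under the arm of the clinic where they enrolled.
- Treat transfer as a reason to seek the outcome by the telephone contact already planned. S-weight is a brief self-report instrument and suits this; BMI, waist and body fat need a visit and may stay missing.
- Report deaths by arm, and do not impute readiness after death.
- Define loss to follow-up identically in both arms as no S-weight response obtained at week 9, keeping any week-5 data.
- State that week-5 and week-9 outcomes are collected whether or not modules are completed. Record module completion separately as adherence.

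The imputation method can be left to the analysis plan. The cost is a few sentences, slightly more follow-up effort and possibly a smaller observed effect. Timing matters: the article expected data collection to start in June 2023 and analysis in 2024. If follow-up has ended, the analysis set can still be corrected before analysis, but outcomes never collected from non-compliers may not be recoverable. Their number should then be reported by arm.

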#### Sample Size Calculation

The sample size was calculated using OpenEpi (version 3; Kelsey et al) open-source calculator for cross-sectional, cohort, and randomized control trials. To obtain 95% CI and 80% power of the study (α=.05), the minimum sample size required in each arm is 44 to achieve a 30% proportion difference postintervention [20]. Considering a 40% (n=21 participants) attrition rate, we aim for a total of 65 participants per arm.

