**Methods:**

A web-based intervention will be developed based on the Transtheoretical Model targeting adults with T2D with obesity who are not ready to change for weight loss. Phase 1 will involve the development and validation of the web-based health intervention module. In phase 2, a nonrandomized controlled trial will be conducted in 2 government health clinics selected by the investigator. This is an unblinded study with a parallel assignment (ie, intervention vs control [usual care] with an allocation ratio of 1:1). A total of 124 study participants will be recruited, of which 62 participants will receive the Chance2Act intervention in addition to the usual care. The primary outcome is the changes in an individual’s readiness from a stage of not being ready to change (precontemplation, contemplation, or preparation stage) to being ready for weight loss (action stage). The secondary outcomes include changes in self-efficacy, decisional balance, family support for weight loss, BMI, waist circumference, and body fat composition.

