### Phase 2: Nonrandomized Controlled Trial

#### Study Setting

Phase 2 of the study will be conducted as a nonrandomized controlled trial, which is aimed to determine the effectiveness of the Chance2Act intervention. The study is expected to be conducted over 4 to 6 months, at 2 government health clinics in Pahang state, Malaysia. These 2 health clinics will be enrolled by the researcher and are expected to have similarities in terms of the sociodemographic background of the local community. The assignment into either the intervention or control group will be based on the health clinic where the participants are getting their treatment from. One health clinic will be assigned as the intervention arm whereas another clinic as the control arm. The study flowchart for phase 2 is summarized in Figure 2. This is an unblinded study with a parallel assignment (ie, intervention vs control [usual care] with an allocation ratio of 1:1). Blinding is not possible due to the nature of the intervention which is mainly health education.

To avoid contamination, the 2 health clinics will not be selected from neighboring localities. Access to the Chance2Act website will be restricted only to the registered participants and family members from the intervention arm. A username and password will be provided to log in to the website. The participants, family members, and the medical staff at the participating health clinics are not allowed to share any intervention material with a third party.

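### The attrition inflation is wrong, the enrolment target is given as both 65 and 62 per arm, and neither leaves the required 44 per arm at the planned 40% loss

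*Protocol article*

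**What the plan says.** The protocol article, Sample Size Calculation, names its tool ("The sample size was calculated using OpenEpi (version 3; Kelsey et al) open-source calculator") and its error rates ("To obtain 95% CI and 80% power of the study (α=.05"). It reports that "the minimum sample size required in each arm is 44 to achieve a 30% proportion difference postintervention". It then allows for attrition: "Considering a 40% (n=21 participants) attrition rate, we aim for a total of 65 participants per arm".

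The Methods paragraph of the abstract gives another number: "A total of 124 study participants will be recruited, of which 62 participants will receive the Chance2Act intervention". The Study Setting section describes the design as "intervention vs control [usual care] with an allocation ratio of 1:1", so the abstract's target is 62 per arm, while the sample size section implies 2 × 65 = 130 in total.

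The Delivery section defines loss to follow-up: "Participants who did not comply with the follow-up requirements will be considered a loss to follow-up".

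**The concern.** Three things look wrong.

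- The 40% rate and the count of 21 are presented as the same quantity, and they do not match on either available base.
- The article carries two enrolment targets, 130 and 124 in total, and nothing in it reconciles them.
- An inflation for attrition exists to leave the required number after the losses. Neither target appears to do that at the rate the plan itself chose.

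Two things are at stake. The 80% power claim rests on 44 per arm remaining, so it fails if the plan's own attrition occurs. And the planned sample size is the figure against which recruitment and the final report are judged, so it has to be one figure.

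**Working it through.** **Inputs from the protocol article.** α = 0.05 (taken as two-sided, given the 95% CI), power 80%, a 30-point difference in proportions, 44 per arm, attrition 40% or 21 participants, and 65 per arm (all Sample Size Calculation); 124 in total with 62 in the intervention arm (abstract); 1:1 allocation (Study Setting).

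**Input that is not given.** The control proportion. It is varied below.

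**Step 1: reproduce the base figure of 44.** The Kelsey formula per arm is n = (z_{α/2} + z_β)² × 2 × p̄(1 − p̄) / d², where p̄ is the mean of the two proportions.

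- 35% v 65% (p̄ = 0.50): (1.96 + 0.842)² × 2 × 0.25 / 0.30² = 43.6, so 44.
- 30% v 60%, or 40% v 70%: 43.2, so 44.
- 20% v 50%: 40.
- 10% v 40%: 33.

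So 44 reproduces for control proportions of about 30% to 40%. It also supports reading the 30% as percentage points.

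**Step 2: try to reproduce the inflation.**

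| Calculation | Result |
|---|---|
| 44 / (1 − 0.40), which preserves 44 | 73.3, so 74 per arm (148 in total) |
| 44 × 1.40, which does not preserve 44 | 61.6, so 62 per arm |
| 40% of 44 | 17.6 |
| 21 / 44 | 47.7% |
| 21 / 65 | 32.3% |

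The 65 is simply 44 + 21, and it follows from neither method. The abstract's 62 is consistent with multiplying by 1.40, although the article does not say how it was obtained.

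**Step 3: number left at 40% attrition.**

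- 65 × 0.60 = 39 per arm, 5 short of 44.
- 62 × 0.60 = 37.2, so 37 per arm, 7 short of 44.

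The highest attrition that still leaves 44 is 1 − 44/65 = 32.3% for 65 per arm and 1 − 44/62 = 29.0% for 62 per arm.

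**Step 4: power with the number left.** Power = Φ( d / √[2p̄(1 − p̄)/n] − 1.96 ). With 35% v 65% and n = 39: 0.30 / √(0.50/39) = 2.65; 2.65 − 1.96 = 0.69; Φ(0.69) ≈ 0.755. The other values are obtained in the same way, and the last column uses the pooled/unpooled variance formula (Fleiss, no continuity correction).

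| n per arm | Kelsey variance, 35% v 65% | Fleiss, 35% v 65% |
|---|---|---|
| 44 | 80.4% | 81.5% |
| 39 | 75.5% | 76.5% |
| 37 | 73.3% | 74.2% |

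Across control proportions of 30% to 40%, the two formulas give 75.5% to 77.0% with 39 per arm and 73.3% to 74.7% with 37.

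**The case against.** The core arithmetic is hard to dispute, so the case for the plan concerns size and emphasis.

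- **The power loss is small.** It is about 3 to 7 points, and only if the full 40% is lost; up to 32% loss, 65 per arm still keeps 44. This stands, and it limits the consequence. It does not make the stated figures right.
- **The methods section governs and the abstract only summarises.** That would favour 65, but the article does not say so, and 65 is not a correct inflation either.
- **The power figures depend on an assumed control proportion.** This is true. With 10% v 40%, Kelsey power would be 86.4% with 39 per arm and 84.6% with 37. But the Kelsey minimum would then be 33, not 44, so that reading contradicts the plan's own minimum instead of rescuing the target.
- **The analysis is by intention to treat with GEE, so everyone counts.** Intention to treat does not supply outcomes that were never measured, and by inflating 44 for attrition the plan itself treats 44 as the number needed after losses. How remaining missing data will be handled is not specified, so no power figure for a particular imputation rule is relied on here.
- **A condensed article may leave the assumed proportions to the full protocol.** Agreed. Their absence is not the complaint; they matter only because the sponsor needs them to restate the power.

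**Conclusion.** The concern holds on all three parts. The inflation is wrong (40% is not 21 participants, and 44 after 40% loss requires 74 per arm). The target is stated two ways (130 and 124 in total). Both targets fall below the plan's own minimum at the plan's own attrition rate (39 and 37 against 44).

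These conclusions need nothing beyond the article's own numbers. The size of the power loss does rest on an assumption, namely proportions near 35% v 65%, the region where the stated method returns 44, with a two-sided test at 0.05. Under it, power at 40% attrition is about 76% with 65 enrolled per arm and about 73% to 74% with 62, against the 80% stated. The effect on power is modest, but a core planning figure is wrong as written and must be corrected.

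**What to change.** Choose one enrolment target and use it in both the abstract and the sample size section. Remove the pairing of 40% with 21 participants. Then take one of two coherent routes.

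1. **Keep 65 per arm and restate what it buys.** Possible wording: 65 per arm (130 in total) retains 44 per arm at up to 32% attrition; at 40% attrition 39 per arm remain, and power for a 30-point difference is about 76%, assuming 35% versus 65%. The sponsor should replace that last figure with one computed from the proportions actually used. If 62 is the real target, the matching figures are 29% attrition, 37 per arm, and about 73% to 74% power.
2. **Keep both the 40% attrition and the 80% power, and enrol 74 per arm (148 in total).** This adds 9 per arm to the target of 65 (18 in total), or 12 per arm to the target of 62 (24 in total).

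The first route costs only wording and a slightly less favourable power statement, and it remains open if recruitment has finished (the article expected data collection to start in June 2023). The second costs extra recruitment and is practical only while enrolment is open.
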